## 5.2 Modified Rankin Score

The Modified Rankin Scale (mRS) is recorded at Day 7, 28, 90 and 180 as well as at discharge. mRS will be analysed as a score ranging from 0-6 as displayed in Table 2. Any patient who has died before the respective timepoint will be given a score of 6. Any mRS recorded at the discharge visit that is contained within the protocolled defined time-windows and is closer to the nominal time than any other recordings will be used at that timepoint.

**Table 2. Modified Rankin Score (mRS)**

| mRS recorded response                                                                                                       | Score assigned for analysis |
|-----------------------------------------------------------------------------------------------------------------------------|-----------------------------|
| No symptom at all                                                                                                           | 0                           |
| No significant disability despite symptoms; able to carry out all usual duties and activities                               | 1                           |
| Slight disability; unable to carry out all previous activities, but able to look after own affairs without assistance       | 2                           |
| Moderate disability; requiring some help, but able to walk without assistance                                               | 3                           |
| Moderately severe disability; unable to walk without assistance and unable to attend to own bodily needs without assistance | 4                           |
| Severe disability; bedridden, incontinent and requiring constant nursing care and attention                                 | 5                           |
| Dead                                                                                                                        | 6                           |

## 5.3 Glasgow Outcome Score Extended

The Glasgow Outcome Scale – Extended (GOSE) is recorded at Day 28, 90 and 180. GOSE will be analysed as a score ranging from 1-8 as displayed in Table 3. Any patient who has died before the respective timepoint will be given a score of 1.

**Table 3. Glasgow Outcome Scale – Extended (GOSE)**

| GOSE recorded response    | Score assigned for analysis |
|---------------------------|-----------------------------|
| Death                     | 1                           |
| Vegetative state          | 2                           |
| Lower severe disability   | 3                           |
| Upper severe disability   | 4                           |
| Lower moderate disability | 5                           |
| Upper moderate disability | 6                           |
| Lower good recovery       | 7                           |
| Upper good recovery       | 8                           |

## **5.4 Incidence of Delayed Cerebral Ischaemia**

Delayed Cerebral Ischaemia (DCI) is defined as a new focal deficit or reduction in Glasgow Coma Scale  $\geq 2$  if not explained by other causes (i.e. re-bleed, hydrocephalus, seizure, meningitis, sepsis or hyponatremia). Patients with the following MedDRA terms will be examined as part of a blinded medical review to decide whether the patient has had a DCI satisfying the outlined criteria:

Delayed ischaemic neurological deficit  
Cerebral ischaemia

It is possible additional patients will be identified in a blinded fashion based on other terms.

## **5.5 Incidence of New Cerebral Infarct**

Patients with the following MedDRA terms will be examined as part of a blinded medical review to determine whether the patient experienced a new cerebral infarct on Computed Tomography (CT) or Magnetic Resonance Imaging (MRI):

Cerebral infarction  
Haemorrhagic cerebral infarction  
Thrombotic cerebral infarction  
Haemorrhagic stroke  
Ischaemic stroke  
Thrombotic stroke  
Basal ganglia stroke  
Brain stem stroke  
Cerebral thrombosis

It is possible additional patients will be identified in a blinded fashion based on other terms.

## **5.6 Triple H therapy**

The dedicated Triple H Therapy for Cerebral Vasospasm CRF will be used to determine for each patient whether such therapy was received.

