**Table 1. TCD Recordings**

| Reading                                           | Units/Response |
|---------------------------------------------------|----------------|
| Left Middle Cerebral Artery Mean Flow Velocity    | cm/s           |
| Right Middle Cerebral Artery Mean Flow Velocity   | cm/s           |
| Left Internal Cerebral Artery Mean Flow Velocity  | cm/s           |
| Right Internal Cerebral Artery Mean Flow Velocity | cm/s           |
| Assessment Performed                              | Pre/Post       |
| Lindergaard Ratio Left                            | none           |
| Lindergaard Ratio Right                           | none           |

The primary endpoint is defined as the maximum of all left middle cerebral artery mean flow velocities (MCA-MFV) and right MCA-MFV values recorded after the first dose of randomised therapy including any taken after Day 7.

Baseline values will be defined as:

- The lowest of the left and right MCA-MFV values recorded at the earliest TCD assessment made within 2 days of first dose
- If a patient does not have a TCD recorded within 2 days of dosing, a predicted baseline value will be imputed based on their age, WFNS score (1 to 5), a past medical history of hypertension (yes/no), surgical procedure (clipping, coiling, none), log-CRP and centre as described below.

Amongst patients with baseline values recorded within 2 days of dosing, their baseline value will be regressed on age, WFNS score, hypertension, surgical procedure, log-CRP and centre. The imputed value for patients with a missing baseline value will equal  $\mu + \sum x_{ij}\beta_j$  where  $x_{ij}$  represent the observed values of the  $j$  covariate levels for the  $i^{\text{th}}$  patient and  $\beta_j$  the corresponding parameter estimates from the regression amongst patients with observed baseline values.

Supplementary analyses will also be performed on the mean of the three largest right or left MCA-MFV recorded at any timepoint after dosing. Additionally, an analysis will be performed to describe the effect over time with timepoints grouped, relative to date of Ictus, as Days 3-4, 5-6, 7-9, 10-14, 15-21, 22-28. Within each timepoint the largest MCA-MFV value will be included in the analysis for each patient. For these two analyses, the same baseline as the primary analysis will be used. Using the timepoint analysis the mean effect of Days 5 to 9 will also be estimated.

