### **5.13 Safety Data**

Recording of AEs starts from informed consent and continues until at least 30 days post last dose. The definition of AEs and SAEs are given in the protocol.

Adverse events starting on or after the first treatment dose are therefore defined as Treatment Emergent Adverse Events (TEAEs). Any AE that starts more than 30 days past last dose and is considered to be at least possibly related to study treatment should also be defined as a TEAE. Any event starting before the first dose of study drug is identified as a Pre-Treatment Adverse Event (PTAE). Any event starting before the first dose of study drug that subsequently worsens is also be defined as a TEAE.

All events are coded using the MedDRA dictionary. The actual description of the AE is matched, as closely as possible, with the Lower Level Term in the dictionary.

All AEs are classified as described in Table 10.

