## 6.5 Analysis of Secondary Efficacy Endpoints

The mRS, GOSE, SAHOT and CLCE will be analysed using a proportional odds logistic regression model to each timepoint separately including the following covariates: treatment, age (fitted as continuous variable), WFNS score (fitted as a class variable), hypertension (yes vs no), surgical procedure (clipping vs coiling vs none) and log-CRP. The treatment effect will be described using an odds ratio together with its likelihood ratio based 95% confidence interval. The statistical significance of the treatment effect will be taken from the chi-square test for the difference in deviance when removing treatment from the model. GOSE scores will be reversed prior to analysis so the odds of a better response is being modelled. PROC LOGISTIC can be used to analyse the data. If the model does not converge, any covariates that are not statistically significant will be removed in order from least significant until the model converges. If the model still does not converge, the outcome level with the fewest observations will be combined with the next most severe outcome and this process repeated until convergence is achieved.

BICRO and SF-36 will be analysed using Van-Elteren's test with 4 strata defined by age (above and below the median) and WFNS score (1-3 v 4-5). The treatment effect will be described using an un-stratified Hodges-Lehmann (HL) estimate of median difference together with its 95% confidence interval. The test can be implemented in SAS as follows:

```

proc npar1way data=data1 HL;
  strata strata/wilcoxon;
  class trt;
  var resp;
run;

```

The proportion of patients with delayed cerebral ischaemia, new cerebral infarct and receiving triple H therapy will be analysed using logistic regression with the same set of covariates used for mRS. The statistical significance of the treatment effect will be taken from the chi-square test for the difference in deviance when removing treatment from the model. The treatment

effect will be described in terms of an odds ratio together with its likelihood ratio based 95% confidence interval.

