***Qualifying Evaluations (Surgery, Eligibility And Screening Procedures)***

Dates and times of all qualifying evaluations will be listed as: Onset of Ictus, Surgery (plus WFNS and any Triple H Therapy for Cerebral Vasospasm), Eligibility, Investigator Consent, Randomisation and Dosing. Other reported dates included: Discharge, MRI at follow up and End Of Study (EOS).

The time between Ictus and the patient receiving their first dose of randomized medication will be summarized for both the ITT and PP populations by treatment arm.

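### The Triple H endpoint has no start point, so therapy begun before the first dose would count as an outcome; for DCI and new infarct, pre-dose events are not expressly excluded

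*SAP*

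**What the plan says.** **Triple H.** Section 5.6 consists of one sentence: "The dedicated Triple H Therapy for Cerebral Vasospasm CRF will be used to determine for each patient whether such therapy was received". It has no start date, no end date and no reference to first dose. Table 11 in Section 6.2 lists the endpoint as a proportion of patients.

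**DCI.** Section 5.4 gives a clinical criterion: "Delayed Cerebral Ischaemia (DCI) is defined as a new focal deficit or reduction in Glasgow Coma Scale" of at least 2 points, if other listed causes do not explain it. Patients with certain MedDRA terms are flagged, and a blinded medical review decides.

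**New infarct.** Section 5.5 works the same way: a list of terms flags patients, and the blinded review is "to determine whether the patient experienced a new cerebral infarct on Computed Tomography (CT) or Magnetic Resonance Imaging (MRI"). The scan or date against which an infarct is new is not stated.

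**Source of the flagged events.** Section 5.13 says: "Recording of AEs starts from informed consent and continues until at least 30 days post last dose". It also sets up a pre-dose class: "Any event starting before the first dose of study drug is identified as a Pre-Treatment Adverse Event (PTAE"). Sections 5.4 and 5.5 do not use that class.

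**Analysis.** Section 6.5 says: "The proportion of patients with delayed cerebral ischaemia, new cerebral infarct and receiving triple H therapy will be analysed using logistic regression". It adds no restriction on timing. Section 7 (Secondary Efficacy Endpoints) plans cumulative incidence plots of time to each event and does not state the time origin.

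**Contrast.** The primary endpoint in Section 5.1 uses left and "right MCA-MFV values recorded after the first dose of randomised therapy including any taken after Day 7".

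**The concern.** A treatment or event that began before the first dose cannot have been caused or prevented by study drug. If it enters the outcome, it adds the same kind of noise to both arms and pulls the odds ratio towards 1. With about 90 evaluable patients, a few such cases can also fall unevenly by chance.

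For Triple H the written rule produces this directly, because any receipt on the form makes the patient an event. For DCI and infarct the rule leaves the decision to the blinded reviewers, who have no stated reference date for what is new.

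All three endpoints are formally tested, and reducing DCI is a named secondary objective in Section 2. If the question first arises after unblinding, the choice of which events count becomes post hoc.

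**Working it through.** **1. Is there a timing rule anywhere?**

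| Endpoint | Source of events | Filter | Tied to first dose? |
|---|---|---|---|
| Maximum MCA velocity (5.1) | TCD recordings | after first dose | Yes |
| TEAEs (5.13) | AE form | on or after first dose, or worsening afterwards | Yes |
| Triple H (5.6) | dedicated CRF | none | No |
| DCI (5.4) | flagged MedDRA terms | blinded review; new deficit or GCS fall | Not stated |
| New infarct (5.5) | flagged MedDRA terms | blinded review; new on imaging | Not stated |

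Sections 6.2, 6.5 and 7 do not change the last column. Every analysed patient has a first-dose date, because the PP and ITT populations in Section 4.1 both require dosing. Event dates are needed anyway for the planned time-to-event plots.

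**2. How large could the effect be?** The SAP gives no event rate for these endpoints and no pre-dose count. Its only power figure, in Section 3.1, concerns TCD velocity, so there is no figure to reproduce. The rates below are assumptions.

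Inputs: 45 per arm (90 evaluable patients from Section 3.1, with 1:1 allocation assumed); two-sided 5% (Section 6.1); the same pre-dose share q in both arms.

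Observed rate: p = q + (1 − q) × post-dose rate.

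Odds ratio: OR = [p_T/(1 − p_T)] / [p_C/(1 − p_C)].

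Power, unadjusted normal approximation: Φ[(|p_C − p_T| − 1.96·SE0)/SE1], with SE0 from the pooled rate and SE1 from the separate rates.

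Example with 30% v 15% and q = 5%:
- p_C = 0.05 + 0.95 × 0.30 = 0.335, and p_T = 0.05 + 0.95 × 0.15 = 0.1925.
- OR = (0.1925/0.8075)/(0.335/0.665) = 0.47.
- SE0 = √(0.26375 × 0.73625 × 2/45) = 0.0929.
- SE1 = √[(0.335 × 0.665 + 0.1925 × 0.8075)/45] = 0.0917.
- Power = Φ[(0.1425 − 0.1821)/0.0917] = 33%.

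| Assumed post-dose rates (control v SFX-01) | q = 0 | q = 2% | q = 5% | q = 10% |
|---|---|---|---|---|
| 20% v 10% | OR 0.44, power 26% | 0.49, 24% | 0.54, 21% | 0.60, 17% |
| 30% v 15% | OR 0.41, power 40% | 0.44, 37% | 0.47, 33% | 0.52, 28% |
| 35% v 15% | OR 0.33, power 59% | 0.35, 56% | 0.39, 51% | 0.43, 44% |
| 40% v 20% | OR 0.38, power 55% | 0.39, 52% | 0.42, 48% | 0.46, 42% |

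**3. Could a chance imbalance look like an effect?** Assume no true effect, 11 of 45 (24%) with an event in each arm, and three pre-dose patients all in one arm.
- Some of the three would have had a post-dose event anyway, so the expected addition is 3 × 34/45 = 2.27, giving 13.27 of 45.
- OR = (13.27/31.73)/(11/34) = 1.29.
- SE(log OR) = √(1/11 + 1/34 + 1/13.27 + 1/31.73) = 0.48.
- z = 0.256/0.477 = 0.54, two-sided p about 0.59.

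Even this one-sided placement is well within ordinary chance variation.

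**The case against.** **The protocol or the CRF may settle the start point.** Section 1 says design details found in the protocol were generally removed, and the Triple H form may accept only therapy begun on study. Section 7 also speaks of Triple H being instituted, which suggests a dated start. This may well be so. But Section 1 also says this version adds detail on endpoint derivations, and the derivation in Section 5.6 is a plain yes or no on receipt.

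**A reader might infer that DCI and infarct count any occurrence.** The SAP does not say that. The MedDRA terms only flag patients. A blinded reviewer must then find a new deficit, GCS fall or infarct, and could reject a pre-dose event. What remains is the absence of an express exclusion.

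**A reader might infer that the plan treats Triple H as both a baseline item and an outcome.** Section 7 (Qualifying Evaluations) lists "Surgery (plus WFNS and any Triple H Therapy for Cerebral Vasospasm), Eligibility, Investigator Consent, Randomisation and Dosing", and Surgery Details tabulates it beside WFNS. But the former paragraph goes on to dates of discharge, follow-up MRI and end of study, so it is not a list of pre-dose items. Neither place names the form from which the item comes. Double use is not established.

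**The exposure is probably short.** Patients present within 48 hours of ictus, and for DCI and infarct the interval at issue runs only from consent to first dose. Section 6.4 says many baseline TCD values were taken shortly after dosing, which suggests prompt dosing. This stands and limits the likely size.

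**These endpoints carry little weight.** Section 6.3 names only mRS and GOSE at 90 days as key secondary endpoints. This also stands.

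**Conclusion.** The point holds for Triple H as the text is written: a start before first dose would be an outcome event. For DCI and new infarct it holds only as an omission, because pre-dose events are not expressly excluded.

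The expected consequence is dilution. On the assumed rates above, a 2% pre-dose share moves the odds ratio by about 0.02 to 0.04 and costs about 3 percentage points of power. A 5% share moves it by about 0.04 to 0.09 and costs about 6 to 8 points. These figures rest on assumed event rates, an equal pre-dose share in both arms, 1:1 allocation and an unadjusted comparison. The true share is unknown and probably small.

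It would be tempting to call this a bias that could create a treatment effect. The documents do not support that: pre-dose events arise before any drug effect, in a randomised double-blind trial, so they balance on average. The point does not touch the primary endpoint or the key secondary endpoints.

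**What to change.** - **Section 5.6:** count Triple H as an event only if it started after the first dose of study medication. Say explicitly how a patient already receiving it at first dose is classified.
- **Sections 5.4 and 5.5:** have the blinded review count only events with onset after first dose, which also gives new a reference point.
- **Section 7:** report any Triple H, DCI or infarct before first dose by arm as background data, and start the cumulative incidence plots at first dose.

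The cost is about a sentence in each place and a date filter on data that the time-to-event plots already need. The event count may fall slightly. The change should be made before unblinding.

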## **5.7 SF-36 Quality of Life Survey**

The SF-36 Quality of Life Survey is recorded at Day 28, 90 and 180. There are 36 questions in the SF-36 survey each of which are recoded into a value between 0 and 100 as presented in Table 4 where 100 represents the best outcome.

**Table 4. SF36 recoding individual responses**

| Item Numbers         | Recorded Response Category | Recoded Score |
|----------------------|----------------------------|---------------|
| 1, 2, 20, 22, 34, 36 | 1 →                        | 100           |

## EVG001SAH Statistical Analysis Plan

|                                 |     |     |
|---------------------------------|-----|-----|
|                                 | 2 → | 75  |
|                                 | 3 → | 50  |
|                                 | 4 → | 25  |
|                                 | 5 → | 0   |
| 3, 4, 5, 6, 7, 8, 9, 10, 11, 12 | 1 → | 0   |
|                                 | 2 → | 50  |
|                                 | 3 → | 100 |
| 13, 14, 15, 16, 17, 18, 19      | 1 → | 0   |
|                                 | 2 → | 100 |
| 21, 23, 26, 27, 30              | 1 → | 100 |
|                                 | 2 → | 80  |
|                                 | 3 → | 60  |
|                                 | 4 → | 40  |
|                                 | 5 → | 20  |
|                                 | 6 → | 0   |
| 24, 25, 28, 29, 31              | 1 → | 0   |
|                                 | 2 → | 20  |
|                                 | 3 → | 40  |
|                                 | 4 → | 60  |
|                                 | 5 → | 80  |
|                                 | 6 → | 100 |
| 32, 33, 35                      | 1 → | 0   |
|                                 | 2 → | 25  |
|                                 | 3 → | 50  |
|                                 | 4 → | 75  |
|                                 | 5 → | 100 |

Using these recoded scores, the Physical Health and Mental Health Score will be derived as follows:

1. 35 of the 36 items will be assigned to one of eight subscales as defined in Table 5 and the mean of the recoded scores,  $\bar{X}_i$  ( $i=1$  to 8), calculated within each subscale, noting that Item 2 is not assigned to a subscale.
2. A Z score for each subscale,  $Z_i$  ( $i=1$  to 8), will then be derived as

$$Z_i = \frac{\bar{X}_i - x_i}{sd_i}$$

where  $x_i$  and  $sd_i$  are the population reference means and standard deviations for a healthy population. Table 6 displays the appropriate reference means.

3. Each  $Z_i$  is multiplied by the corresponding Physical Health coefficient and summed to give an overall Physical Health Sum. The same approach is applied to the Mental Health coefficients to give an overall Mental Health Sum
4. The Physical Health and Mental Health Scores are then calculated by multiplying the respective Physical Health and Mental Health Sum by 10 and adding 50 to the product. A patient with responses typical of a general population will have a score of 50 and perfect health would correspond to Physical Health and Mental Health Scores of 57.87 and 62.14 respectively.

Whilst reference means for a US population are to be applied it has been shown that their application to a UK population gives nearly identical results for the Physical Health and Mental Health Score compared to the use of UK specific reference means.

Any patient who has died before the respective timepoint will be assigned a 0 recoded score for each item of the SF-36 prior to deriving the Physical Health and Mental Health Scores.

If less than 50% of the SF-36 questions are completed at a given timepoint or no responses are completed for an individual subscale, the SF-36 data will not be included in the analysis for that patient at that timepoint. If  $\geq 50\%$  of the SF-36 questions are completed, the mean of the observed individual item recorded scores within the respective subscales will be applied to the algorithm.

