**Table 6. SF-36 Reference Values and Physical and Mental Health Coefficients**

| Subscale | Mean  | SD    | PH Coefficient | MH Coefficient |
|----------|-------|-------|----------------|----------------|
| PF       | 84.52 | 22.89 | 0.42402        | -0.22999       |
| RP       | 81.20 | 33.80 | 0.35119        | -0.12329       |
| RE       | 81.29 | 33.03 | -0.19206       | 0.43407        |
| VT       | 61.05 | 20.87 | 0.02877        | 0.23534        |
| EW       | 74.84 | 18.01 | -0.22069       | 0.48581        |
| SF       | 83.60 | 22.38 | -0.00753       | 0.26876        |
| BP       | 75.49 | 23.56 | 0.31754        | -0.09731       |
| GH       | 72.21 | 20.17 | 0.24954        | -0.01571       |

PH = Physical Health, MH=Mental Health

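### Scoring every SF-36 item as 0 for patients who died does not place death at the bottom of the Physical and Mental Health Scores, so some survivors can rank below the dead

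*SAP*

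**What the plan says.** SAP Section 5.7 scores the SF-36 in steps. There are 36 questions, "each of which are recoded into a value between 0 and 100", with 100 the best outcome. Items are averaged into eight subscales. Each subscale is standardised against Table 6, whose means and SDs "are the population reference means and standard deviations for a healthy population". Each standardised value "is multiplied by the corresponding Physical Health coefficient and summed to give an overall Physical Health Sum", and the Mental Health Sum is built in the same way. The final scores come from "multiplying the respective Physical Health and Mental Health Sum by 10 and adding 50 to the product".

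For deaths, the section states that the patient "will be assigned a 0 recoded score for each item of the SF-36 prior to deriving the Physical Health and Mental Health Scores". The floor is thus set on the items, before the weighting, and not on the scores that are analysed.

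Table 6 contains coefficients of both signs. For example, the physical functioning row reads "PF | 84.52 | 22.89 | 0.42402 | -0.22999": the last figure, the Mental coefficient, is negative.

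In Section 6.5, "BICRO and SF-36 will be analysed using" Van Elteren's test, with an unstratified Hodges-Lehmann estimate of the difference.

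The other outcome scales set death at the worst value of the analysed score itself: mRS 6 (5.2), GOSE 1 (5.3), CLCE-24 3 (5.8), BICRO-39 5 (5.9) and SAHOT category 9 (5.10).

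**The concern.** Setting all items to 0 looks like a way to make death the worst outcome. It would do so if every subscale entered the summary score with a positive weight. In Table 6, however, role-emotional (RE), emotional well-being (EW) and social functioning (SF) carry negative Physical coefficients. Physical functioning (PF), role-physical (RP), pain (BP) and general health (GH) carry negative Mental coefficients. A 0 on one of these subscales adds points, so the dead are credited for having the worst possible value.

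The Van Elteren test works on ranks within strata, and the Hodges-Lehmann estimate works on pairwise differences between arms. Both depend on where the dead sit relative to the living. If survivors in one arm are placed below deaths in the other, those comparisons count against the arm in which the patients survived. The rule applies to both scores at Days 28, 90 and 180, and no SF-36 sensitivity analysis in Table 11 changes it.

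**Working it through.** **Inputs.** Means, SDs and coefficients are from SAP Table 6, and the algorithm is from Section 5.7:

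Score = 50 + 10 × Σ coefficient × (subscale mean score − reference mean) / reference SD.

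**Reproducing the SAP's figures.** With all eight subscales at 100, the formula gives Physical 57.87 and Mental 62.14, exactly the perfect-health values in Section 5.7. With all subscales at their reference means it gives 50.00 and 50.00, also as stated. The table and formula have therefore been read correctly.

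**Death, all items 0.** Each subscale contributes −10 × coefficient × mean / SD:

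| Subscale | Mean / SD | Physical | Mental |
|---|---|---|---|
| PF | 84.52 / 22.89 | −15.66 | +8.49 |
| RP | 81.20 / 33.80 | −8.44 | +2.96 |
| RE | 81.29 / 33.03 | +4.73 | −10.68 |
| VT | 61.05 / 20.87 | −0.84 | −6.88 |
| EW | 74.84 / 18.01 | +9.17 | −20.19 |
| SF | 83.60 / 22.38 | +0.28 | −10.04 |
| BP | 75.49 / 23.56 | −10.17 | +3.12 |
| GH | 72.21 / 20.17 | −8.93 | +0.56 |
| Sum | | −29.86 | −32.66 |
| 50 + sum | | **20.14** | **17.34** |

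The parts are rounded, and the totals come from unrounded values. The negative coefficients add 4.73 + 9.17 + 0.28 = 14.2 points to the dead patient's Physical score. They add 8.49 + 2.96 + 3.12 + 0.56 = 15.1 points to the Mental score.

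**Lowest attainable living score.** Put the negatively weighted subscales at 100 and the rest at 0. Moving a subscale from 0 to 100 changes the score by 1000 × coefficient / SD.
- Physical (RE, EW, SF at 100): −5.81 − 12.25 − 0.34 = −18.40 from rounded parts. Unrounded, the score falls from 20.14 to **1.73**.
- Mental (PF, RP, BP, GH at 100): −10.05 − 3.65 − 4.13 − 0.78 = −18.61 from rounded parts. Unrounded, the score falls from 17.34 to **−1.26**.

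These minima need floors and ceilings at the same time and are bounds, not typical patients.

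**Less extreme profiles below death.** All values are possible under Tables 4 and 5. Start from the dead patient's score and add 10 × coefficient × subscale score / SD.
- Severe physical impairment, preserved mood: PF 0, RP 0, RE 100, VT 40, EW 80, SF 50, BP 30, GH 25. Physical = 20.14 − 5.81 + 0.55 − 9.80 − 0.17 + 4.04 + 3.09 = **12.0**, about 8 points below death. The same patient's Mental score is 61.1.
- Severe emotional impairment, preserved function: PF 90, RP 100, RE 0, VT 15, EW 20, SF 12.5, BP 80, GH 60. Mental = 17.34 − 9.04 − 3.65 + 1.69 + 5.40 + 1.50 − 3.30 − 0.47 = **9.5**, again about 8 points below death. The same patient's Physical score is 63.1.

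**Profiles that stay above death, or nearly so.**
- PF 0, RP 0, RE 33, VT 40, EW 60, SF 50, BP 50, GH 40: Physical 22.9.
- PF 0, RP 0, RE 0, VT 30, EW 40, SF 25, BP 50, GH 40: Physical 27.3, Mental 32.1.
- PF 90, RP 100, RE 0, VT 30, EW 40, SF 50, BP 80, GH 60: Mental 21.1.
- PF 0, RP 0, RE 100, VT 40, EW 80, SF 50, BP 62.5, GH 45: Physical 18.9, only just below death.

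**The case against.** The strongest defence is that death still scores about 30 points below the general-population value of 50 on both scales, so in most comparisons with survivors it ranks lower. The profiles that fall below it are polarised: the first example has near-perfect mental health (61.1 against 62.14), and the second has a Physical score above the perfect-health value (63.1 against 57.87). Mixed impairment stays above death. All of this stands, and it limits the size of the problem.

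A reader might infer that any severely disabled or severely depressed survivor ranks below the dead, or that a mortality benefit would show up as harm. The SAP does not support either reading. Only some profiles are affected, and nothing in the document says how many patients would have them.

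A reader might also infer that the SAP breaches its own stated requirement. It does not: Section 5.7 never says that death must be the worst SF-36 outcome. That intent is inferred from the all-zero rule and from the death rules of the other scales. What is shown is an inconsistency with those rules.

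Finally, SF-36 is neither the primary endpoint nor one of the two key secondary endpoints (Section 6.3). It is analysed at first only in the per-protocol population (Section 6.2), which leaves out patients who die before receiving 10 doses. Deaths are placed at the worst value for mRS and GOSE and are also reported separately (Section 7). The main conclusions do not rest on this rule. None of this alters the arithmetic.

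**Conclusion.** The concern holds in a limited form. As written, the rule gives the dead 20.14 and 17.34, which is 18.4 points (20.14 − 1.73) and 18.6 points (17.34 + 1.26) above the lowest attainable living scores. Some survivors with polarised profiles can rank below death, which can partly misdirect the Van Elteren test and the Hodges-Lehmann estimate.

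The scores follow from the SAP's own algorithm, which reproduces its published check values, and need no outside assumption. Calling the rule a defect assumes that death is meant to be the worst outcome here, as it is for mRS, GOSE, CLCE-24, BICRO-39 and SAHOT. The practical effect depends on the number of deaths and of polarised survivors in each arm and stratum, which cannot be determined from the SAP. It should be corrected, as a secondary-endpoint matter.

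**What to change.** In Section 5.7, delete the item-level 0 rule. State instead that a patient who died before the timepoint receives one fixed value directly on each summary score, strictly below the attainable minimum: for example 0 for Physical (below 1.73) and −2 for Mental (below −1.26).

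In Section 6.5, state that the same values enter both the Van Elteren test, where they act as tied worst ranks, and the Hodges-Lehmann estimate. Specifying only a tied worst rank is not enough, because the Hodges-Lehmann estimate is a median of pairwise numerical differences and needs a number. Add a note that this estimate and its interval may depend on the value chosen.

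The cost is a sentence or two in each section and a small programming change, with no new data. If the all-zero rule is kept on purpose, Section 5.7 should say that death is not meant to rank last on these scores, and why.
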